#### Interim analysis

One interim analysis, with the option to stop for efficacy or futility, is planned after outcomes are available for 50% of the patients. Stopping for efficacy at the interim analysis is based on the O’Brien-Fleming type alpha-spending function, which corresponds to a significance level of 0.0054 (two-sided) if the interim analysis is at exactly 50% of the planned sample size. Early stopping is only considered when the O’Brien-Fleming criteria are met for both the analysis on the full population and the subgroup with prenatal diagnosis. Statistical testing at completion will follow the same hierarchy, at the O’Brien-Fleming adjusted two-sided alpha level. The overall type I error remains controlled at the 5% two-sided, in view of the hierarchical procedure. An independent statistician and a data monitoring committee (DMC) have access to the interim results. The DMC will advise the principal investigator on the continuation of the trial. The principal investigator is responsible for deciding to continue, modify, or terminate the trial.

#### Secondary analysis

Secondary analysis is based on the comparisons of secondary outcomes between the allopurinol and mannitol-placebo group, both for the total study population and separately for subgroups of CCHD. Additionally, a secondary analysis will be performed to assess an interaction with gender, as females possibly benefit more from allopurinol administration than males [30]. Descriptive statistics will be applied, including the independent sample *t*-test or the Mann-Whitney *U*-test for continuous data and Pearson’s chi-square test for categorical data. Safety analyses will be based on incidences of (serious) adverse events in both groups.

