Prior animal and small neonatal studies suggest neuro- and cardioprotective effects of allopurinol [25]. Clancy et al. showed that the use of perioperative allopurinol resulted in a lower composite rate of clinical seizures, cardiac events, coma, and death in infants with hypoplastic left heart syndrome [26]. During intracardiac repair for tetralogy of Fallot, allopurinol had beneficial effects on the use of inotropes, duration of mechanical ventilation, and intensive care stay [24]. Postnatal administration of allopurinol improved neurodevelopmental outcomes in infants with moderate hypoxic-ischemic encephalopathy [27–29]. Neuronal injury, as measured by S100B and neuroketal levels, was reduced after antenatal administration of allopurinol to fetuses suspected of hypoxia, especially in females. No severe side effects of allopurinol were observed in all previously performed neonatal studies, and neither in the currently ongoing ALBINO Study (NCT03162653) [24, 26–33]. Only in 4.5% of mothers receiving allopurinol, reversible irritation of perivascular tissue was reported after intravenous administration [30].

Previous neuroprotective research in neonatal CCHD focused mainly on interventions exclusively in the perioperative period. However, brain injury occurs already preoperatively [8, 34, 35]. Pretreatment with neuroprotective drugs as allopurinol, which blocks the cascade to ischemic brain lesions, should therefore be administered both early after birth and around cardiac surgery with CPB. Additionally, pre- and postoperative brain MRI are needed to evaluate the effects of postnatal and perioperative treatments on brain lesions separately. Perioperative MRI can be used as a “bridging biomarker” for long-term neurodevelopmental outcomes, since it is known that moderate to severe ischemic brain injury is associated with poorer outcomes at school-age [36].

Therefore, this phase III, randomized, quadruple-blinded, placebo-controlled, multicenter trial will evaluate CeRebrUm and CardIac protection with ALlopurinol in neonates with CCHD Requiring Cardiac Surgery with CPB (CRUCIAL). The aim of this study is to reduce moderate/severe ischemic and hemorrhagic brain injury and improve cardiac function and neurodevelopmental outcomes in CCHD children.

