#### Prenatal group

In neonates that are diagnosed with CCHD before birth, allopurinol PFI or mannitol-placebo PFI 20 mg/kg body weight per administration will be administered early postnatally (within 45 (max. 60) min after birth and 12 h after the first dose), preoperatively (12 h prior to cardiac surgery), intraoperatively (at the start of CPB), and postoperatively (24 h after surgery) (Fig. 1).

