#### Postnatal group

Neonates in whom CCHD is diagnosed after birth will only receive the pre-, intra-, and postoperative doses of allopurinol PFI or mannitol-placebo PFI (Fig. 1).

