#### Secondary outcomes

The secondary outcomes that will be compared between the allopurinol and mannitol-placebo groups are presented in Table 1 and include the five elements (domain, specific measurement, specific metric, method of aggregation, and time point) as described by Zarin et al. and Saldanha et al. [55, 56].

**Table 1 Tab1:** Secondary outcomes

Domain	Specific measurement	Specific metric	Method of aggregation	Time point
Brain injury severity	Brain injury severity score, determined by the assessment of brain injury on MRI in the deep gray matter, white matter, cortex, and cerebellum [39, 40].	Preoperative brain injury severity score, postoperative brain injury severity score, and change between pre- and postoperative brain injury severity score	Mean (and SD) or median (and IQR) per group	Preoperative (4–7 days after birth) Postoperative (5–10 days after surgery or at least within 1 month after surgery)
White matter injury volume	White matter injury volume (mm^3^), determined by manual segmentation with 3D-Slicer or ITK-SNAP 2.0 [41–43].	Preoperative white matter injury volume, postoperative white matter injury volume, and change between pre- and postoperative white matter injury volume	Mean (and SD) or median (and IQR) per group	Preoperative (4–7 days after birth) Postoperative (5–10 days after surgery or at least within 1 month after surgery)
Echocardiographic systolic and diastolic function	Echocardiographic assessment of global ventricular function (normal, mildly reduced, moderately reduced, severely reduced); ejection fraction (%); shortening fraction (%); ventricular dimensions (mm, *Z*-score corrected for BMI); velocity over the cardiac valves, i.e., *V*peak (m/s) and *V*mean (m/s); cardiac valve insufficiency (no, mild, moderate, severe); longitudinal strain (%) and tissue Doppler imaging (myocardial deformation indices (m/s)); and systolic and diastolic pulmonic vein flow (m/s) [44].	Preoperative echocardiographic measurements, postoperative echocardiographic measurements, and change between pre- and postoperative echocardiographic measurements	Distribution per group for categorical variables and mean (and SD) or median (and IQR) per group for continuous variables	Preoperative (4–7 days after birth) Postoperative (5–10 days after surgery or at least within 1 month after surgery)

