#### Brain MRI

Brain MRI will be performed pre- and postoperatively on a 1.5- or 3.0-T MRI scanner to assess the presence, severity, and volume of ischemic and hemorrhagic parenchymal brain lesions. The MRI scanning protocol includes at least T1-, T2-, diffusion-, and susceptibility-weighted imaging and MR venography [8, 39, 41]. Preoperative MRI will take place within 4–7 days after birth or at least preoperatively. Postoperative MRI will take place preferably within 5–10 days after surgery or at least within 1 month following CPB.

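### Preoperative MRI and echocardiography are compared by arm in the total population, although most postnatally diagnosed neonates will not yet have had study drug; the early-dose effect is diluted by up to a fifth

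*Protocol article*

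**What the plan says.** The Secondary analysis section sets the population for all secondary outcomes: "Secondary analysis is based on the comparisons of secondary outcomes between the allopurinol and mannitol-placebo group, both for the total study population". The sentence goes on to add subgroups, so that the populations in full are "both for the total study population and separately for subgroups of CCHD". The subgroups are not defined. The methods are unadjusted: "Descriptive statistics will be applied, including the independent sample *t*-test or the Mann-Whitney *U*-test for continuous data", with a chi-square test for categorical data.

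Table 1 (Secondary outcomes) lists, for MRI severity, "Preoperative brain injury severity score, postoperative brain injury severity score, and change between pre- and postoperative brain injury severity score". White matter injury volume and echocardiography have the same three metrics. No row is limited to one diagnosis group.

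Dosing differs by group. Prenatally diagnosed neonates receive two doses early after birth, then a third "preoperatively (12 h prior to cardiac surgery"), then intraoperative and postoperative doses. Postnatally diagnosed neonates "will only receive the pre-, intra-, and postoperative doses of allopurinol PFI or mannitol-placebo PFI". On imaging, the Brain MRI section says "Preoperative MRI will take place within 4–7 days after birth or at least preoperatively".

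The Background gives the purpose of scanning twice: "pre- and postoperative brain MRI are needed to evaluate the effects of postnatal and perioperative treatments on brain lesions separately".

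**The concern.** The same variable has a different status in the two groups. In the prenatal group a day 4–7 scan follows two doses, so it is an outcome of the early treatment. In the postnatal group it usually precedes any study drug, so it is a baseline and the arms should differ there only by chance. A pooled test of the preoperative value therefore averages a possible effect with a near-certain zero.

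The change score has a related problem. In the prenatal group it starts from a value that treatment may already have lowered; in the postnatal group it starts from a mostly untreated value. One pooled comparison of change estimates neither the early nor the perioperative effect.

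At stake is the answer on the early doses, which the Background presents as the reason for treating before as well as around surgery.

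**Working it through.** **Inputs.** From the Sample size section: 236 neonates, 188 prenatal and 48 postnatal; assumed control event rates 71% and 55%; absolute reductions 20 and 9 points; two-sided alpha 5%; power about 80%. Equal arms are taken from the Risk and benefit section (half receive placebo). The document gives no effect size, SD or pre/post correlation for secondary outcomes, so those below are assumptions. The 12 h timing is stated for the prenatal group; I read it across to the postnatal group, whose schedule is in a figure not available to me.

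**1. The plan's own figure.** With w = 188/236 = 0.797:
- control rate = 0.797 × 0.71 + 0.203 × 0.55 = 0.6775
- allopurinol rate = 0.797 × 0.51 + 0.203 × 0.46 = 0.4998
- difference = 0.1776
- standard error at 118 per arm: 0.0641 pooled, 0.0630 unpooled
- power = Φ[(0.1776 − 1.96 × 0.0641)/0.0630] = 79.6% (80.5% with unpooled variance throughout)

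The stated design reproduces.

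**2. Dilution of a preoperative effect.** If no postnatal-group neonate is dosed before the measurement, the total-population effect is w × (prenatal effect) + (1 − w) × 0 = 0.797 of the prenatal effect, a loss of 48/236 = 20.3%. Information scales with effect squared times sample size: 0.797² × 236 ≈ 150 neonates, against 188 in the prenatal group alone.

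**3. Power, continuous outcome** (equal SD in both groups assumed). The effect giving 80% power with 94 per arm is (1.960 + 0.842) × √(2/94) = 0.409 SD. The total population sees 0.797 × 0.409 = 0.326 SD, and power = Φ[0.326/√(2/118) − 1.96] = 70.6%. Regaining 80% in the mixed population would need 298 neonates. Where the prenatal-only power is 70% or 90%, the pooled power is 60.2% or 82.5%.

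**4. Power, binary illustration.** Take 30% preoperative lesions as the control rate in both groups (the Background's upper figure for ischemic lesions) and an assumed 15% on allopurinol in the prenatal group. The difference falls from 15.0 to 11.9 points, and power from 69.5% (188) to 57.5% (236).

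**5. If some postnatal-group scans follow the preoperative dose.** Let a share f be measured after dosing and show the full effect. The retained effect is 0.797 + 0.203f.

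| f | Effect retained | Pooled power at 0.409 SD |
|---|---|---|
| 0 | 79.7% | 70.6% |
| 25% | 84.7% | 75.8% |
| 50% | 89.8% | 80.5% |

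Pooling and restricting have equal power when the retained effect is √(188/236) = 0.893, that is, f = (0.893 − 0.797)/0.203 ≈ 47%. Pooling costs power unless about half of the postnatal group is measured after the dose with full effect.

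**6. Change score.** Let a be the effect on the preoperative value in the prenatal group, and b₁ and b₂ the effects on the postoperative value in the prenatal and postnatal groups. The between-arm effect on change is b₁ − a in the prenatal group and about b₂ in the postnatal group. The pooled test estimates 0.797(b₁ − a) + 0.203b₂.

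**7. Use of the pre-dose value in the postnatal group.** Relative to analysing the postoperative value alone, with equal variances and assumed pre/post correlation ρ, the variance of change is 2(1 − ρ) and of ANCOVA 1 − ρ².

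| ρ | Change | ANCOVA |
|---|---|---|
| 0.3 | 1.40 | 0.91 |
| 0.5 | 1.00 | 0.75 |
| 0.7 | 0.60 | 0.51 |

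**The case against.** The best reply is that the plan already provides the right comparison. Elsewhere, including the Sample size section and the Discussion, the article uses the word subgroup for prenatal versus postnatal diagnosis, so the subgroup analyses may include the prenatal-only contrast. That is possible. But the phrase could equally mean type of cardiac defect; the Discussion does not tie its prenatal analysis to the secondary outcomes; and the diluted total-population test stays in place either way.

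Second, the choice of population and covariates for each secondary outcome often sits in the SAP, which is not shown. The article, however, states a population and tests for all secondary outcomes, so this is something fixed badly rather than left out.

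Third, the pooled contrast is randomised and does not inflate false positives. That stands: the cost is attenuation, lost power and a mixed estimand.

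Fourth, if lesions simply accrue, change measures new injury and serves the stated aim. Within the prenatal group change is indeed a valid randomised contrast. Reading it as the perioperative effect alone needs the further assumption that later injury does not depend on earlier injury or earlier doses, and the article does not argue for that.

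Three stronger readings are tempting but unsupported:
- That no postnatal-group neonate has had drug by the preoperative scan. The MRI window stays open until surgery, so some scans may follow the preoperative dose.
- That postnatal aEEG and NIRS are diluted too. The participant timeline marks procedures by diagnosis group, but the figure is not available; if only prenatally diagnosed neonates are monitored after birth, there is no dilution.
- That the baseline is wasted. Planned change scores do use it, though less efficiently than adjustment would, and without separating the groups.

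**Conclusion.** The point holds for preoperative MRI and echocardiography. The total-population comparison understates the early-dose effect by up to 20%, an upper bound reached only if no postnatal-group measurement follows dosing. Under the assumed 0.409 SD, power falls from 80% in 188 neonates to about 71% in 236. The pooled change score has no clean interpretation, contrary to the purpose the Background gives for the two scans. The 20% follows from the document's own group sizes; the power and variance figures rest on the stated assumptions.

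A reader might infer that the primary analysis is also compromised, or that it should be stratified by preoperative injury. The documents do not support that. The primary endpoint is assessed after surgery, its sample size already assumes a smaller effect in the postnatal group, and any gain from such a stratum would be small and depend on assumed prevalences. This is a correction to secondary analyses, worth making before unblinding.

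**What to change.** State the following in the Secondary analysis section or the SAP:

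- Between-arm comparisons of preoperative MRI and echocardiography use the prenatal stratum (n = 188). Apply the same rule to postnatal aEEG and NIRS only if these are also done in the postnatal group. Randomisation is stratified by diagnosis timing, so the restriction keeps the randomised comparison.
- In the postnatal group, analyse the postoperative value by ANCOVA with the pre-dose preoperative value as covariate, instead of raw change. Count a value as baseline only if it was obtained before the first dose.
- In the prenatal group, do not adjust postoperative results for the on-treatment preoperative scan, and do not present pre-to-post change as an isolated perioperative effect.
- Define which subgroups the section means.

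Total-population comparisons of postoperative values stay as planned. The cost is wording, plus the time of each postnatal-group scan relative to first dose. The downside is that the preoperative comparisons use 188 rather than 236 neonates, and the ANCOVA rests on at most 48.

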Seizure activity	Presence or absence of seizure activity on aEEG [45, 46].	Postnatal seizure activity and postoperative seizure activity	Proportion of neonates with seizure activity per group	Postnatal (until at least 24 h after birth) Postoperative (until at least 48 h after surgery)
Regional cerebral oxygen saturation	Regional cerebral oxygen saturation (%), lowest regional cerebral oxygen saturation (%), and duration of regional cerebral oxygen saturation < 45% (minutes) will be assessed by NIRS in intervals 0–3, 3–6, 6–12, 12–24, and 24–36 h after birth and 0–3, 3–6, 6–12, 12–24, 24–48, and 48–72 h after surgery [47, 48].	Postnatal regional cerebral oxygen saturation, postoperative regional cerebral oxygen saturation, and change between postnatal and postoperative regional cerebral oxygen saturation	Mean (and SD) or median (and IQR) per group	Postnatal (until at least 24 h after birth) Postoperative (until at least 48 h after surgery)
General movements	Assessment of general movements, using the motor optimality score [49–51].	Motor optimality score at 3 months	Mean (and SD) or median (and IQR) per group	3 months
Motor, cognitive, and speech/language development	Motor, cognitive, and language composite score of the Bayley-III-NL. An average Bayley-III-NL score is 100; one SD above or below the mean concerns 15 points [52].	Motor, cognitive, and language composite score at 24 months	Mean (and SD) or median (and IQR) per group and proportion per group below 1 SD	24 months
Quality of life	Parent-reported quality of life score using the TNO-AZL Preschool Children’s Health-Related Quality of Life questionnaire [53].	Parent-reported quality of life score at 24 months	Mean (and SD) or median (and IQR) per group	24 months
Cost-effectiveness of allopurinol	Questionnaires on the need for healthcare resources, productivity losses of parents, and expenses borne by families. Healthcare and societal costs will be determined with the Dutch guidelines for health economic evaluation.	Healthcare and societal costs at 3 months; healthcare and societal costs at 24 months	Mean (and SD) per group	3 months 24 months
Cost-effectiveness of allopurinol	Length of hospitalization and intensive care stay (days) and costs associated with hospitalization using standard unit prices from Dutch guidelines for health economic evaluation.	Healthcare costs	Mean (and SD) per group	24 months

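### The plan does not name the prenatal-diagnosis group as the population for preoperative MRI and echocardiography, so the comparison it does name dilutes the early-dose effect to about 80%

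*Protocol article*

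**What the plan says.** The Secondary analysis section compares all secondary outcomes between allopurinol and placebo "both for the total study population and separately for subgroups of CCHD". It does not say which subgroups are meant, and it sets no separate population for outcomes measured before surgery.

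Table 1 lists for brain MRI: "Preoperative brain injury severity score, postoperative brain injury severity score, and change between pre- and postoperative brain injury severity score". White matter injury volume and echocardiography follow the same pattern. For aEEG it lists "Postnatal seizure activity and postoperative seizure activity", and NIRS is handled likewise.

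Dosing differs by time of diagnosis. The Prenatal group section gives two doses "early postnatally (within 45 (max. 60) min after birth and 12 h after the first dose", and later a dose "preoperatively (12 h prior to cardiac surgery", followed by intra- and postoperative doses. The Postnatal group section says that infants diagnosed after birth "will only receive the pre-, intra-, and postoperative doses of allopurinol PFI or mannitol-placebo PFI".

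The Brain MRI section places the preoperative scan at 4–7 days after birth, or failing that at any time before surgery. The Echocardiography section prefers the same day as the MRI. The Background states why the scans are paired: "pre- and postoperative brain MRI are needed to evaluate the effects of postnatal and perioperative treatments on brain lesions separately".

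**The concern.** The preoperative comparison is the planned way to see what the early doses do before the perioperative doses and surgery itself come into play. In the total population, that comparison mixes infants randomised to early allopurinol or early placebo with infants who receive neither. In the second group the two arms have usually been treated identically up to the assessment, so their expected difference is zero. Including them pulls the estimate towards zero while adding their variance.

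At stake is a missed or understated early effect. The primary analysis is not affected. If the total-population result is read as the answer to the Background's question, a real benefit of the early doses could look smaller than it is. If the prenatal-only result is read instead, nothing in the section says that this was the intended estimate, so the choice could appear to have been made after the results were seen.

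**Working it through.** **The plan's own power figure.** The Sample size section gives 188 prenatal infants (71% falling to 51%) and 48 postnatal infants (55% falling to 46%), with about 80% power for the primary endpoint at a two-sided 5% level.
- Control rate: (188 × 0.71 + 48 × 0.55)/236 = 0.6775.
- Allopurinol rate: (188 × 0.51 + 48 × 0.46)/236 = 0.4998.
- Difference 0.1776 with 118 per arm (1:1 allocation is implied by the Risk and benefit assessment section). The Z-test with pooled variance has 79.6% power, so the stated figure is reproduced.

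The article states no effect size or power for any secondary outcome. What follows is therefore illustrative.

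**Dilution.** Let δ be the early-dose effect in the prenatal group, and assume zero in the postnatal group.
- Share without early doses: 48/236 = 20.3%.
- Expected total-population effect: δ × 188/236 = 0.797δ.

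**Power.** With equal variance in both groups, the expected test statistic is proportional to effect × √n.
- Ratio, total to prenatal-only: (188/236) × √(236/188) = 0.893.
- 80% power in 188: (1.960 + 0.842) × 0.893 − 1.960 = 0.54, giving 70.6% power in 236.
- 90% power in 188: (1.960 + 1.282) × 0.893 − 1.960 = 0.93, giving 82.5%.
- 50% power in 188: 1.960 × 0.893 − 1.960 = −0.21, giving 41.7%.
- Total needed at the same mix to regain the prenatal-only power: 236²/188 = 296.3, or 298 after rounding up to whole infants in two equal arms.

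**A binary example.** The Background reports preoperative ischemic lesions in up to 30%. Assume, for illustration only, 30% falling to 13% in the prenatal group, and a postnatal-group rate of 20–40% that is the same in both arms. Power is 81.5% in the prenatal group alone and 67–72% in the total population.

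**If some postnatal-group scans follow a dose.** Let the postnatal group show a fraction f of the prenatal effect, starting from 80% power in the 188.

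| f | Power in 236 |
|---|---|
| 0 | 70.6% |
| 0.10 | 72.7% |
| 0.25 | 75.8% |
| 0.50 | 80.5% |

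The two analyses break even when 0.797 + 0.203f = 0.893, that is at f of about 0.47. Below that, adding the 48 infants lowers power. Whatever f is, the postnatal group's contribution is not an effect of the early doses.

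**The case against.** The strongest reply is that the same sentence also plans subgroup analyses. Prenatal versus postnatal diagnosis is the split used in the Primary analysis, Interim analysis and Sample size sections. It is a randomisation stratum, and the Discussion calls the prenatal group the main subgroup of interest. An undiluted estimate in 188 infants can be obtained and may well be intended. This stands. A reader might infer that the only direct evidence on the early doses is diluted, and the document does not support that.

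What remains is that the subgroups are undefined. They could equally be the cardiac defect types of the inclusion criteria, or the syndromic subgroup of the Discussion. The Primary analysis section names the prenatal group explicitly for the primary endpoint, and the Secondary analysis section does not. Even on the favourable reading, nothing says which estimate answers the Background's question.

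A reader might also infer that no postnatal-group infant has had any study drug by the preoperative assessment. That is too absolute. A scan may be done at any time before surgery, so some could follow the dose given 12 h before it. None would follow an early dose.

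For birth-phase aEEG and NIRS, the participant timeline marks procedures separately by group, but that figure is not available here. Monitoring after birth may be scheduled for the prenatal group only, in which case nothing is diluted. Nor does the missing-data section say that values from before enrolment would be imputed for the postnatal group, so that inference is not supported either.

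Finally, a comparison of everyone randomised is legitimate in itself. It is biased only when read as the effect of the early doses.

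**Conclusion.** The point holds for preoperative brain injury score, white matter injury volume and echocardiography. The one population the section clearly names for them is unsuited to the purpose that the Background gives the preoperative MRI, and the suitable population is not designated. In the total population the early-dose effect is diluted to about 80% of its size. Power falls by roughly 8 to 9 percentage points from a starting value of 50–90%, despite 48 more infants.

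These figures rest on the planned 188:48 split, equal variance in the two groups, and no drug effect before assessment in the postnatal group; the table above shows how they move if the last assumption fails in part. The error is conservative: it favours finding no effect and does not inflate type I error. It concerns secondary outcomes only and leaves the primary analysis untouched. For birth-phase aEEG and NIRS the point is conditional on both groups being scheduled for them.

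**What to change.** In the Secondary analysis section and Table 1:
- Name the prenatal-diagnosis stratum (planned n = 188) as the main analysis population for preoperative MRI and echocardiography outcomes. Do the same for birth-phase aEEG and NIRS if these are scheduled in both groups.
- State that the CCHD subgroups include prenatal versus postnatal diagnosis, and list any others.
- Report the postnatal group's preoperative values descriptively, by arm.
- Keep the total population for postoperative outcomes, pre-to-postoperative change and later outcomes. The 48 postnatal infants are informative about the perioperative doses, and restricting the change scores would discard them.

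Time of diagnosis is a stratification factor, so the restriction keeps the randomised comparison. The cost is a sentence or two and a table footnote, with no change to data collection. The 48 infants leave the formal preoperative comparison, but they carry no information on the early doses. The wording should be settled before the study team is unblinded.
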